## Methods

### Eligibility criteria

All patients from our five partner clinics with a reliable diagnosis of breast cancer will be included in this study (C50.0–.9 und D05.0–.9). Moreover, the rehabilitants must be between 18 and 60 years old, own a smartphone and have adequate German language skills.

All rehabilitants who do not have a reliable diagnosis of breast cancer or who abandon rehab are excluded from the study. Other criteria for excluding participants are insufficient German language skills, missing declaration of consent and constraints in physical activity.

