Indirect costs reflect the loss of value added due to the illness, valued in monetary units. From a pension insurance perspective, expenditure on rehabilitation and aftercare represents investments in maintaining earning capacity. To this extent, benefits for temporary and permanent reduction in earning capacity should be highlighted here. Costs arising from periods of incapacity to work on the part of the health insurance funds (sick pay) and employers (continued wage payments) and income losses from reduced working hours without financial compensation by the social insurance funds, e.g., reduced earning capacity pensions for female patients, are further cost items to be included. From a societal perspective, lost social security contributions also need consideration. In addition to these work- and employment-related productivity losses, ReNaApp accounts for reductions in performance in private life (e.g., housework, leisure time, voluntary work) to complete the patient perspective.

Two valuation approaches - the human capital approach (HCA) and the friction cost approach (FCA) - are available for determining the costs associated with the performance and productivity reductions. Both reflect the societal perspective, but they account for productivity losses differently. The controversial discussion about the two methodological approaches has not been resolved, so the recommendation to apply both approaches and examine the different outcome effects in sensitivity analyses is followed [67, 68]. Both approaches tend to neglect non-work activities (household, child-rearing, voluntary work, leisure time, etc.). Since it is to be expected that a significant proportion of the ReNaApp target population is already of pensionable age, the limited recording of indirect costs for the periods up to retirement can constitute discrimination. In this respect, a sensitivity analysis is additionally carried out based on the average remaining life expectancy [78].

For the assessment of the loss of value added due to sickness-related absence from work, the average gross annual income from dependent employment for the total working population [74] is applied to obtain results independent of indications.

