### Case number calculation/sample size

According to the time and primary outcomes, we expect that both groups (control and intervention groups) will similarly improve until the end of rehab. In the following period, the effects in the CG will approach the starting level before rehab, while the positive changes in the IG will stabilize and even increase slightly. We assume that the intervention group will return to work with higher likelihood and earlier than the CG.

Regarding the needed sample size, the primary outcome *restriction in participation* (IMET [42]) will be involved. For this purpose, we have results from our own studies about the influence of “Neues Credo”. To determine the effect of data on the Quality Community for Medical Rehabilitation (QGmR, indication oncology) [52], the controlled trial of “Neues Credo” [14] and the feasibility study of “Neues Credo” [15] were taken into account.

The QGmR data from oncological patients who followed a standard rehab and standard aftercare did not show an effect (ES = 0.05) on participation after a four-month follow-up. The IG participation in the controlled trial of “Neues Credo” showed an effect intensity of ES = 0.42 in a 12-month follow-up, and the control group showed an effect intensity of ES = 0.06. Psychosomatic rehabilitants reached an effect intensity of ES = 0.53 for participation after a four-month follow-up in the feasibility study of “Neues Credo”.

Calculating the sample size, we assume clinically relevant and positive effects (pre-catamnesis-ES = 0.40) in *social and work-related participation* (IMET [42]) in the IG after a 12-month follow-up. Compared to the intervention group, the control group does not show any effects to the point of catamnesis. The other two primary outcomes are expected to show comparable effect intensity [79–81]. To demonstrate differences between the IG and CG after a 12-month follow-up, we require a magnitude of ES = 0.40 by double-sided testing with α = 1.6% (Bonferroni correction for three primary outcomes) with a power of 80%. That is why the intervention and control groups need a net sample size of *n* = 235 for each. We expect a dropout rate of 30% from patients with oncological rehab (according to experiences in QGmR oncology). To analyse each group of n = 235 patients, we must initially recruit 336 participants for the study; i.e., every rehab clinic has to recruit 112 participants (56 participants in each group).

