### Statistical methods

#### Quantitative analysis

The longitudinal data will be analysed by variance analysis with repeated measurements; the nominal and ordinal scaled parameters will be evaluated by analysis of contingency tables; the subgroup analysis will be carried out with qui-square tests and t-tests.

The primary outcome *return to work* will be retrospectively captured with a questionnaire after 12 months. The rehabilitants will provide information regarding whether they returned to work after rehab and how much time passed between rehab and the return to work. The time until the return to work is collected in models of survival analysis for discrete times. The entire analysis will be carried out with SPSS 22.0.

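### Return to work, a co-primary outcome, has no stated risk set and no power basis of its own; separately, the pensionable-age premise conflicts with the 18 to 60 age limit

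*Protocol article*

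**What the plan says.** **Outcome and analysis.** The Primary outcome section lists participation (IMET), breast cancer-specific quality of life and return to work. Return to work is captured at 12 months with two items: whether the woman went back to work after rehabilitation and, if so, after how many months. The items are put to the rehabilitants without restriction by work status. Under Quantitative analysis, "The time until the return to work is collected in models of survival analysis for discrete times". No risk set is given.

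**Eligibility.** By age, "the rehabilitants must be between 18 and 60 years old". The other conditions concern diagnosis, smartphone, language, consent, completion of rehabilitation and constraints in physical activity. None concerns employment or sick leave.

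**Sample size.** The calculation rests on IMET ("Regarding the needed sample size, the primary outcome" is restriction in participation). It uses "we require a magnitude of ES = 0.40 by double-sided testing"; the level and power are "double-sided testing with α = 1.6% (Bonferroni correction for three primary outcomes) with a power of 80" per cent, with a net 235 per group. Return to work and quality of life are covered by one sentence: "The other two primary outcomes are expected to show comparable effect intensity". No return rate, hazard ratio or share at risk is given.

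**Health economics.** Cost parameters of the study expects that "a significant proportion of the ReNaApp target population is already of pensionable age", and on that ground adds a sensitivity analysis based on average remaining life expectancy.

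**The concern.** Return to work can only happen to a woman who is in the labour force and not working when rehabilitation starts. The criteria also admit women who are already working and women who are not in the labour force. If everyone who answers the item is analysed, these women appear as never returned or as returned at once. Neither says anything about the intervention, and both pull the groups together. If they are left out, the number analysed is below the 235 on which the calculation rests.

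Recruitment is sequential, with the control group filled first (section A, quantitative measures), so the mix of work status could also differ between groups over calendar time. At stake is one of three primary tests, to which a third of the error rate has been assigned.

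The pensionable-age sentence is a separate problem. It describes a sample that the age limit does not allow, and a planned economic analysis is justified by it.

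**Working it through.** **Step 1: the plan's own figure.** Inputs from Case number calculation/sample size: ES 0.40, two-sided α = 0.016, power 80%.

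n per group = 2(z₁₋α/₂ + z₀.₈₀)² / ES² = 2(2.409 + 0.842)² / 0.40² = 132.1, so 133. This is not the stated 235. ES 0.30 gives 234.8, so 235. The later steps do reproduce: 235/0.7 = 336, and 336 × 1.1 = 370.

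**Step 2: the continuous scale.** Power = Φ(ES·√(n/2) − 2.409). The share at risk is not in the article; 100%, 80% and 60% are assumptions, giving n = 235, 188 and 141 per group.

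| ES | n = 235 | n = 188 | n = 141 |
|---|---|---|---|
| 0.40 | 97% | 93% | 83% |
| 0.30 | 80% | 69% | 54% |

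At ES 0.40, power stays at 80% or more until the share falls below 133/235 = 57%. At ES 0.30, any loss takes it below 80%.

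**Step 3: return to work as a yes/no outcome.** A standardised difference of 0.40 corresponds to an odds ratio of exp(0.40 × π/√3) = 2.07. The control return rate p₁ is not in the article; 50%, 70% and 80% are assumptions.

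Power = Φ(|p₂ − p₁|/SE − 2.409), with SE = √{[p₁(1 − p₁) + p₂(1 − p₂)]/n}.

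Example, p₁ = 0.70: odds 2.333 × 2.066 = 4.820, so p₂ = 4.820/5.820 = 0.828. With n = 235, SE = 0.0387, 0.128/0.0387 = 3.31, and power = Φ(0.90) = 82%.

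Only women at risk analysed:

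| Control rate → intervention rate | 100% at risk (235) | 80% (188) | 60% (141) |
|---|---|---|---|
| 50% → 67% | 93% | 86% | 73% |
| 70% → 83% | 82% | 71% | 56% |
| 80% → 89% | 65% | 53% | 40% |

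**Step 4: all 235 analysed, women not at risk included.** With share f at risk, the proportions become f·p if the others count as non-returners, or f·p + (1 − f) if they count as returned. At p₁ = 0.70 and f = 0.80 these are 0.560 v 0.663, or 0.760 v 0.863.

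| Control rate 70% | Others counted as non-returners | Others counted as returned |
|---|---|---|
| 80% at risk | 45% | 68% |
| 60% at risk | 23% | 50% |

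Both codings are below the 71% and 56% obtained by analysing only women at risk, although more women are counted.

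**Step 5: pensionable age.** The eligibility section ends at 60. The cost section expects a significant proportion to be of pensionable age already. The article does not state that age; read in its ordinary sense, as old-age pension, it lies above 60. Pensions for reduced earning capacity, mentioned in the same section, can be drawn earlier, but the sentence speaks of age. The two statements cannot describe one sample.

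**The case against.** A reader might infer that return to work will be analysed in all 235 per group. The article does not say so. Asking every woman the item does not fix the analysis set, and an article may leave the risk set to a full protocol or analysis plan that is not shown. That stands: the codings in step 4 are possibilities, not the plan. What remains is what the article does fix: this outcome shares the split error rate, and the 235 is extended to it by an assumed equal effect, with no condition making those 235 women eligible for the event.

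A reader might also infer that the 80% power fails. That does not follow. On the continuous scale at ES 0.40 there is a margin down to about 57% at risk, and at a 50% control rate power is still 86% with 80% at risk. The margin does not simply carry over to a yes/no and time outcome, however. If ES 0.30 lies behind the 235, there is none. The control rate matters as much as the share at risk: at 80%, power is 65% even with every woman at risk. The Secondary outcomes section itself says that many patients go back to work without major problems.

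The Limitations section provides for comparing the groups and adjusting by covariates or propensity score matching. This answers much of the concern about imbalance, though work status is not among its examples. It does not remove the dilution.

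Finally, a reader might conclude that the life-expectancy analysis should be dropped. It also addresses losses after retirement and neglected non-work activity, which concern women under 60 too. Only its stated rationale is wrong.

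**Conclusion.** The point holds in limited form. For return to work, the 80% power is neither derived nor established. Over the assumed ranges (60 to 100% at risk, control return rate 50 to 80%, odds ratio 2.07, α = 1.6%), it runs from 93% down to 40% when only women at risk are analysed. Including the others as non-returners or immediate returners lowers it further; at a 70% control rate it is 45 to 68% with 80% at risk. These figures use a two-proportion test as a stand-in for the discrete-time model, and the share at risk and the return rate are assumptions. They show what the power depends on and do not prove a shortfall.

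The conflict between the age limit and the pensionable-age premise needs no assumption beyond the ordinary meaning of the term. It has no bearing on the power of the primary outcome.

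**What to change.** 1. Restrict the return-to-work analysis to women who are in the labour force and not working at the start of rehabilitation, identified from the baseline work and sociodemographic items in Table 1. Describe the other women separately. Whether job-seeking women belong in the set is a choice of estimand; the wording here includes them.
2. Confirm that those baseline items record employment and sick-leave status. Table 1 does not show this. If they do not, a question is needed.
3. State that the 80% power applies to IMET, and give a range for return to work over plausible shares at risk and control return rates. Since 235 corresponds to ES 0.30 and not 0.40, correct that in the same paragraph.
4. Reconcile the pensionable-age sentence with the 18 to 60 criterion, and reword the reason for the life-expectancy sensitivity analysis, which can stay.

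The cost is wording and a less favourable power statement. No new patients are needed, and no new data if the baseline items hold work status.

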#### Qualitative analysis of the interviews and focus groups

The interviews and focus groups will be evaluated by qualitative content analysis [63, 82–84]. The program MAXQDA 12 accompanies the evaluation. The transcripts will be reviewed for relevant topics and interesting content to finally develop a category system. The main topics will be deduced from the research questions and the interview guideline; subcategories will be induced from materials, for example, developed by subsumption [82]. To test the category system first, an independent test coding will be performed by two scientists; afterwards, the categories and definitions will be modified. The whole coding process will be developed in the form of a consensual coding [84], i.e., the transcripts will be independently coded by two scientists. Last, the coding will be merged to develop a consensus.

## Discussion

According to the wishes of oncological patients, this intervention enables a supportive, home-based, and need-based aftercare programme.

The regular practices of physical activity have high curative potential for people with chronic and degenerative diseases [85]. Against the background of demographic change, the number of chronically ill people increases; thus, more support in carrying out physical activity is necessary. Furthermore, in the future, almost all rehabilitants will own a smartphone, making possible the widespread use of ReNaApp.

### Innovation factor

Currently, no aftercare programme for oncological patients exists. Despite the legal situation, oncological patients need to continue exercising after rehabilitation. However, the conditions at home make the realization of recommendations for exercise difficult despite the increased motivation though rehab.

Nevertheless, the aftercare concept “Neues Credo” is a valid strategy for chronically ill people to engage in more physical activity. Developing this strategy according to the growing importance of digitization, it is necessary to modify the concept from paper-based materials into a mobile application. Finally, digitalization offers new solutions for the healthcare sector.

Most of the patients who live in rural areas are disadvantaged regarding specific aftercare services. A mobile application offers the opportunity of an equal aftercare programme to all patients.

Last, this concept develops through a participative process. Focus groups comprising breast cancer patients and conversations with members of breast cancer self-aid groups supported a high interest and need for this application. In addition, the whole study processes will be accompanied by patient representatives to safeguard the user perspective and individual expectations and wishes. This strategy aims to exploit the potential of ReNaApp. The app can positively affect permanent integration in everyday life. Under this consideration, we expect the rehabilitants to indicate a high usability and very good acceptance regarding ReNaApp.

### Immediate expected results of the project

The use of ReNaApp for 12 months leads to clinically relevant and positive effects (pre-post-ES > 0.40) in different primary outcomes after rehab. In addition to a significant increase in social and work-related participation in the IG, breast cancer patients in the IG return faster and more often to work than patients following the standard aftercare programme. This is accompanied by lower indirect costs in the IG. Furthermore, the quality of life increases.

The extent of restriction in social and work-related participation and the quality of life of the control group are comparable to the conditions of the intervention group at the beginning of rehab. Additionally, the participants in the control group returned to work less often and later than participants in the intervention group.

Compared to the CG participants, IG participants using ReNaApp show significant positive effects in all secondary outcomes 1 year after rehab. This includes less physical, psychological and occupational stress as well as a better prognosis of employment and work ability.

Last, the intervention group shows differences compared to the control group regarding a significantly stronger extent of physical activity 1 year after rehab. Unlike the patients in the control group, the breast cancer patients in the intervention group more often engage in self-engaged fitness training or sports programmes though the ReNaApp; they practice significantly more endurance sports.

### Transferability of the project results to the everyday care situation

The aftercare concept “Neues Credo”, modified as a mobile application, aims to maintain the long-term effects of rehab of oncological rehabilitants. Focussing on high individual responsibility, the strategy also targets greater empowerment and self-control of the rehabilitants. During rehab, the participants are trained in these strategies. Afterwards, the rehabilitants transform into their own motivators and the experts of their own aftercare.

The advantage of the new strategy is the time and financial relief for aftercare agents gained because of an integrated self-control and motivational feedback tool. The only temporal expenditure for the clinics regards sending motivation letters to the patients and, if necessary, providing contact in case of questions.

The intervention ReNaApp will be implemented and evaluated in five oncological rehab clinics for breast cancer patients in Germany. In general, it is possible to transfer the intervention to other clinics. Undoubtedly, the developed mobile application could be adapted and expanded for other diseases. Thus, this app could support all people needing support in home exercise.

To secure the transfer to mobile technology, information and materials are compiled for cost units and rehab clinics.

### Limitations

First, it is possible that the disease worsens during and after rehabilitation. In this scenario, patients could contact their aftercare agents and review the personal aims and plans for physical activity and adapt them to the new situation.

In the technical part of the study, the risk of failure of the mobile application exists. In this case, we have the chance to consult our experts of IMIS and ITM to, e.g., provide new updates for the application.

Personal data will never be transferred from the application to the study leader or aftercare agents. ReNaApp keeps the information, statistics and documentation private.

To ensure equal treatment for the IG and CG, all characteristics of the participants (e.g., age, education) and the disease (e.g., disease severity, disease status, and comorbidity) will be documented and compared between the groups. If differences arise between the two groups, they will be comparably integrated in the analysis (e.g., as covariates in multivariate methods or by propensity score matching). Based on our present knowledge, we assume that structural changes in the context of this project are very unlikely.

## Data Availability

The datasets generated and/or analysed during the current study are not publicly available due to the data protection regulations and declarations of consent of the study participants but are available from the corresponding author on reasonable request. The declarations of consent do not include the release of the data for external analyses. A sample declaration of consent is available from the corresponding author on request. The study results are published and thus made available to all those interested in the study. It is not planned to make the individual participant data (IPD) available. The study protocol, the dataset at the participant level and the statistical code for generating the results will also not be made publicly available.

## Abbreviations

AQUAM: Arbeitsgruppe qualitativer Methoden is a German Working group on qualitative methods
CG: Control group
FCA: Friction cost approach
HCA: Human capital approach
ICF: International Classification of Functioning, Disability and Health
ID: Identification number
IG: Intervention group
IPD: Individual participant data
PSM: Propensity score matching
PWA: Progressive web application
QALYs: Quality adjusted life years
QoL: Quality of life
RCT: Randomized clinical trials
